In a paper published in 2016, Markin discusses some common errors made in the treatment of perinatal grief after a miscarriage, including minimizing or avoiding painful affects related to the miscarriage, assuming that the patient’s grief will be resolved in case of a subsequent healthy pregnancy, and neglecting early unresolved losses that are reawakened by the miscarriage [6]. The international literature is in agreement that there is significant psychological morbidity associated with miscarriage. Anxiety, depression and post-traumatic stress disorder PTSD have all been studied in women after miscarriage. According to a review of the literature by Farren et al. in 2018, anxiety is the most common and most persistent psychological disorder after miscarriage [7]. Immediately after a miscarriage, 41% of women present diagnostic criteria for anxiety, with significantly higher scores than in a peripartum control group [8, 9], while at one month after miscarriage, the proportion of women with anxiety was also found to be higher than in a control group [10]. In reported studies, anxiety scores tend to normalize after around 6 months, compared to non-pregnant women [11–13]. However, anxiety may persist up to 12 months after miscarriage, compared to women who had a live birth [7, 14]. Depressive syndrome is diagnosed within 2 weeks after miscarriage in 22 to 36% of women across various studies [8, 12, 15, 16]. Similarly, in women who have had a miscarriage, the relative risk of having a diagnosis of depression was 3 to 4 times higher than in a control group of non-pregnant women [7, 15–17]. The risk of depression is thought to decrease progressively over the first month, although Bergner et al. found that depressive symptoms increased during the first trimester after miscarriage [18]. Finally, PTSD was identified in 25% of women at one month after miscarriage, and in 6% at 4 months in another study [19]. In a study by Farren et al. reported in 2020, at 9 months after a miscarriage, the proportion of women with psychological disorders was 17% for anxiety, 5% for depression, and 16% for PTSD [20].

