### Sample size

The following hypotheses were used to calculate the sample size required for the present study:

A percentage of women with anxiety at 3 months after randomization equal to 22% in the control group (without early psychological care) [20].A percentage of women with anxiety at 3 months after randomization equal to 13% in the intervention group (with early psychological care) (based on the average rate observed in populations with no history of miscarriage).

At an alpha risk of 5% and with power of 90%, in a bilateral situation, the number of subjects needed is 373 per group, i.e. a total of 746 participants. Allowing for 20% of patients lost to follow-up at 3 months after randomization, total accrual of 932 women (466 per group) is planned. Assuming a consent rate of 20%, it is estimated that study information will have to be provided to around 5,000 women in total.

Sample size calculations were performed using NQuery software version 4.0.

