### Randomization

Randomization will be performed only after written informed consent has been obtained. Block randomization will be performed using a computer generated randomization algorithm using SAS software (Version 9.4, SAS Institute Inc., Cary, NC, USA). Participants will be assigned to either the intervention group or the control group in a 1:1 ratio, balancing across 2 factors, namely, randomization will be stratified by parity (with vs. without children) and by use of medically assisted reproduction (with vs. without medically assisted reproduction). It is expected that women who have never yet had a live birth and those who become pregnant via medically assisted reproduction may have a more painful psychological experience of miscarriage.

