#### Secondary outcomes

Depression will be evaluated using the Beck Depression Inventory - Second Edition (BDI-II) [41, 42]. The BDI-II is a self-reported index of depressive symptoms experienced in the past 2 weeks. The questionnaire includes 21 items relating to depression symptoms and attitudes. Answers are on a 4-point scale from 0 to 3 (0 = not at all bothered; 3 = severely bothered). The minimum score is 0 and the maximum is 63. Total score indicates that depression is minimal (from 0 to 11 points), mild (from 12 to 19 points), moderate (from 20 to 35 points), or severe (from 36 to 63 points). For the purposes of this study, presence of depression is defined as a score of 19 or higher, i.e. mild, moderate or severe depression.

The possible presence of post-traumatic stress disorder will be evaluated using the Posttraumatic stress disorder Checklist Scale (PCLS) [43]. The PCLS is a short self-report inventory assessing the 3 main syndromes of PTSD, namely intrusion (intrusive feelings and imagery, dissociative-like re-experiencing, flashbacks); avoidance (numbing of responsiveness, avoidance of feelings, situations, and ideas); or hyperarousal (anger, irritability, hypervigilance, difficulty concentrating or sleeping, heightened startling). The PCLS is a questionnaire containing 17 items assessing the intensity of 17 symptoms over the course of the previous month. Responses are ranked from 1 (not at all) to 5 (very often), yielding a total score ranging from 17 to 85. A score of 44 or more identifies PTSD.

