#### Statistical analysis

Descriptive analysis will be performed. Quantitative variables will be expressed as the mean ± standard deviation or median (range) and qualitative variables as number (percentage). The primary endpoint (presence of anxiety at 3 months after randomization) will be compared between groups using the chi square or Fisher’s exact test, as appropriate. For the secondary endpoints:

presence of anxiety at 6 months after randomization, depression at 3 and 6 months, and PTSD at 3 and 6 months will also be compared between groups using the chi square or Fisher’s exact test, as appropriate.numerical scores for anxiety at 3 and 6 months, and depression at 3 and 6 months after randomization will be compared between groups using the Student t test.

A p-value of < 0.05 will be considered significant. Statistical analysis will be performed using SAS version 9.4 (SAS Institute Inc., Cary, NC, USA).

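### PTSD is the only outcome with no score comparison, although the PCLS total is collected; at the 6% rate cited for 4 months the yes/no test alone has about 35% power

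*Protocol article*

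**What the plan says.** The Statistical analysis section of the protocol gives two lists for the secondary endpoints. The first compares presence of anxiety (6 months), depression (3 and 6 months) and PTSD (3 and 6 months) by chi-square or Fisher's exact test. The second is a t test on scores: "numerical scores for anxiety at 3 and 6 months, and depression at 3 and 6 months after randomization will be compared between groups". The PCLS does not appear in the second list.

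The Secondary outcomes section describes the PCLS as 17 items "yielding a total score ranging from 17 to 85" and sets PTSD at 44 or more. Study procedures has the PCLS completed, with the STAI and BDI, at an initial call within 7 days after randomization and again at 3 and 6 months. Secondary objectives lists PTSD at 3 months and at 6 months among its five items.

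The Background cites three PTSD rates after miscarriage: 25% at one month, then "in 6% at 4 months in another study", and 16% at 9 months. The Sample size section covers the primary endpoint only and assumes no PTSD rate or effect.

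**The concern.** The two lists treat the three outcomes differently without explanation. Anxiety and depression get a yes/no test and a score comparison; PTSD gets only the yes/no test. Reducing a 17-85 score to one cut-off discards every difference on either side of 44. It costs most when few women reach the cut-off.

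If PTSD at 3 and 6 months is near the 6% figure, a non-significant result would say little about whether the sessions help, and there would be no pre-specified score estimate to set beside it. The article fixes which scores will be compared, so a PCLS comparison added after the data are seen would look post hoc. The trial hopes to inform recommendations, and PTSD is one of the three disorders it names.

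**Working it through.** **Inputs**
- Two-sided alpha 5%, power 90%, 373 per group (Sample size: "At an alpha risk of 5% and with power of 90%, in a bilateral situation, the number of subjects needed is 373 per group").
- Planned anxiety rates of 22% and 13% (Sample size), so a risk ratio of 13/22 = 0.591.
- 1:1 allocation (Randomization); 932 women, 466 per group, before 20% loss (Sample size).
- PTSD rates of 6%, 16% and 25% (Background).
- *Assumption:* the effect on PTSD equals the planned risk ratio for anxiety. The protocol gives no PTSD effect, so alternatives follow in step 3.

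**1. Reproduce the stated sample size.** With p̄ = (0.22 + 0.13)/2 = 0.175:

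n = [1.960·√(2·0.175·0.825) + 1.282·√(0.22·0.78 + 0.13·0.87)]² / 0.09² = (1.053 + 0.684)² / 0.0081 = 372.5, rounded up to 373. This matches. 746/0.8 = 932.5, against 932 stated; the difference is immaterial.

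**2. Power of the yes/no PTSD test, 373 per group.**

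Power = Φ{ [|p₁−p₂|·√n − 1.960·√(2p̄(1−p̄))] / √(p₁(1−p₁) + p₂(1−p₂)) }

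| Cited control rate | Rate × 13/22 | Numbers put in | Power |
|---|---|---|---|
| 6% (4 months) | 3.5% | (0.474 − 0.591)/0.301 = −0.39 | 35% |
| 16% (9 months) | 9.5% | (1.264 − 0.924)/0.469 = 0.73 | 77% |
| 25% (1 month) | 14.8% | (1.975 − 1.106)/0.560 = 1.55 | 94% |

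Simulation of the same test gave 34%, 77% and 94%. With all 466 per group analysed, power is 42%, 85% and 98%.

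The 4-month figure is the only cited rate that falls between the two visits: one month from the first and two from the second. The 1-month figure is two months from the first visit, and the 9-month figure three months from the second.

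**3. Other assumed effects at the 6% rate.** Same odds ratio as planned for anxiety: 43%. PTSD halved: 51%. Same shift on an underlying normal scale: 56%. For 80% power the rate would have to fall from 6% to 2.0%, a reduction of about two thirds. Halving gives 92% at 16% and 99% at 25%.

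**4. What a score comparison might gain.** Suppose the step 2 change came from a uniform shift d of a normal score, so that d is the difference between the two normal quantiles. Power of a comparison of means = Φ(d·√(373/2) − 1.960). Because PCLS may be skewed, the table also takes d at half that size.

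| Control rate | d (SD) | Yes/no test | Score, full d | Score, half d |
|---|---|---|---|---|
| 6% | 0.251 | 35% | 93% | 40% |
| 16% | 0.319 | 77% | 99% | 59% |
| 25% | 0.372 | 94% | >99% | 72% |

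Under the normal model the score has a large advantage. At half the shift it keeps a small one at 6% and loses at 16% and 25%. The gain therefore depends on the distribution, and the protocol gives no PCLS distribution.

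**The case against.** The strongest reply is that the choice can be defended. The objectives speak of symptoms of anxiety and of depression but of PTSD as a condition, and the PCLS section says that 44 or more identifies it. Comparing presence for a disorder and scores for symptoms fits that wording, and both PTSD objectives have a stated test. This explains how the asymmetry could arise, but the protocol does not offer it as a reason, and the Discussion itself speaks of symptoms of PTSD. It does support keeping the yes/no analysis.

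The second reply is scope. This is a condensed article, an analysis plan may exist, and supportive analyses are often placed there. That plan could already include the PCLS score. The point still stands against the article, because the article lists the scores to be compared and omits one.

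A reader might infer that the trial can hardly detect any PTSD effect, or that a null result is likely whatever the truth. The documents do not support this. Only one of the three cited rates is low; at the other two, power is 77% and 94% for the planned relative effect. Nor is PTSD clearly the rarest outcome: in the 9-month study that the Background reports for all three disorders, depression is at 5%, PTSD at 16% and anxiety at 17%.

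A reader might also infer that the score is certain to be the better measure. The half-shift column shows otherwise.

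**Conclusion.** The point holds in a limited form. PTSD alone lacks a score comparison, the data for one are collected, and no reason is given. At the cited rate closest in time to the visits, the yes/no test has about 35% power for the planned relative effect (35% to 56% across the effects tried). At the other two cited rates it is adequate or nearly so.

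These figures rest on an assumed PTSD effect, on 373 women analysed per group, and on published rates from other studies carrying over to this trial. The score advantage also rests on the shape of the PCLS distribution. PTSD is a secondary outcome for which no power is claimed, so the primary conclusion is untouched. The change is worth making because it costs almost nothing, not because the trial is at risk without it.

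**What to change.** Add to the listed score comparisons the between-group difference in PCLS total score at 3 months and at 6 months. Report it alongside the yes/no analysis at 44, not in its place, as a supportive estimate with a skewness-robust or bootstrap 95% confidence interval. Adjust for the two randomization strata: parity and medically assisted reproduction.

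Do not describe baseline PCLS as measured before allocation. Study procedures places it within 7 days after randomization, and women are also told their group by phone after randomization. Adjust for it only where it was completed before the woman was told her group.

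Record the addition before outcome data are examined by group; the Study progress section expects data collection to end in January 2026.

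Cost: one phrase in the analysis section or analysis plan and one model fitted at two visits, with no new data. The downside is two more secondary estimates, to which no significance claim should be attached.

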### Study progress

The study began enrollment in July 2023 and the target enrollment of 932 women is expected to be completed by July 2025. Data collection is expected to be completed by January 2026.

### Ethical approval

This protocol was approved by the Ethics Committee of Brest Ouest VI (26/01/2023 under the number 22.04193.000135) and by the national data privacy commission (Commission Nationale de l’Informatique et des Libertés) on 29/03/2023. The protocol will be conducted according to the principles of the Declaration of Helsinki and in line with the Guidelines for Good Clinical Practice. The trial is registered with ClinicalTrials.gov under the identifier NCT05653414 (first registered December 15th, 2022).

## Discussion

Psychological care for women who experience spontaneous pregnancy loss in France is considered to be suboptimal, as in many countries. However, the medical community is becoming increasingly aware of this gap in care, which has garnered substantial attention since 2021, and notably since a series of publications on this topic in *The Lancet* [2, 3, 24]. Despite the fact that abundant data in the literature concur that psychological disorders are unfortunately common and often severe after miscarriage, the available literature does not yield a scientifically validated consensus about the optimal management for this specific situation. We therefore believe that there is a compelling need to generate new and scientifically robust results, to provide evidence-based efficacy data regarding the management of psychological disorders in women who have experienced miscarriage, particularly in the French context.

Our working hypothesis is that a short course of early counselling after miscarriage (i.e. within a few weeks immediately following the miscarriage), could help to reduce the proportion of women who suffer from symptoms of anxiety, depression or PTSD after pregnancy loss. The literature suggests that the intensity of these symptoms is at its peak in the first weeks after miscarriage. Therefore, we chose to include in this randomized, controlled trial women who had experienced a miscarriage within the previous 30 days. We also hypothesized that a short course of counselling, with a maximum of 4 sessions of 45 min each, delivered by teleconsultation with a psychologist, would yield a clinically measurable benefit, as assessed by validated instruments (the STAI-Y for anxiety, the BDI for depression and the PCLS for PTSD). According to Barat et al., brief supportive psychotherapy was effective in reducing symptoms of anxiety, depression and grief in women with miscarriage when conducted in the first 24 h of hospitalization, as compared to a control group [31]. Our randomized, controlled trial was designed taking into account the recommendations issued by the WHO regarding flexibility in terms of scheduling of appointments and the care offered, as well as respect for women’s privacy. Accordingly, there will be no out-of-pocket expenses for any of the participants in this study, which will enable the majority of participants to participate, if they so desire, regardless of their socio-economic status or living circumstances.

The inclusion and follow-up visits will be performed by telephone or video-conference, and the intervention itself (psychological counselling) will also be delivered by teleconsultation. Each participant will have a wide range of choices in terms of days and times, in order to adapt to the individual needs and constraints of each (e.g. work schedules, home life etc.), as well as their possible life circumstances (e.g. desire to keep the miscarriage or counselling secret from family members etc.).

Regarding the evaluation of the endpoints, the questionnaires can be completed in paper format and returned by post, or may be completed online or by email. We chose to perform the inclusion visit and to deliver the intervention via telemedicine, in order to limit potential bias related to certain women being more frequently in contact with the healthcare system, or having their own transport, as this could be to the detriment of the inclusion of women in vulnerable socio-economic situations, or who are isolated, or living in rural or underserved areas. We also aim for the study to integrate, as seamlessly as possible, the real-life context of women experiencing miscarriage.

The design and implementation of this study were made possible by the considerable advances in telemedicine delivery made by primary care professionals during the COVID pandemic. In France, teleconsultation is now fully integrated into routine practice, for both patients and healthcare professionals, as a new form of consultation, accessible to the vast majority of people via smartphone, tablet or computer, and allowing for secure exchange of medical information. All the investigators participating in the study are experienced in the delivery of telehealth.

In summary, this study aims to validate the clinical utility of a short course of early psychological care after miscarriage, based on primary care and accessible to all women, with a view to reducing the burden of psychological disorders after early spontaneous pregnancy loss. The results may form the basis for new recommendations for the management of women who experience miscarriage, notably by recommending the involvement of trained psychologists in the management pathway for early pregnancy loss.

## Data Availability

Not applicable.

## List of abbreviations

BDI: Beck Depression Inventory
GP: General practitioner
PCLS: Posttraumatic stress disorder Checklist Scale
STAI-Y: State-Trait Anxiety Inventory version Y
PTSD: Post-traumatic stress disorder
WHO: World Health Organization
